# Protocol for a hybrid type 3 effectiveness-implementation trial of a pragmatic individual-level implementation strategy for supporting school-based prevention programming

**DOI:** 10.1186/s13012-023-01330-y

**Published:** 2024-01-02

**Keywords:** Individual determinants, Implementation strategy, Theory of planned behavior, Health action process approach, Education sector, Mental and behavioral health

## Abstract

**Background:**

For approximately one in five children who have social, emotional, and behavioral (SEB) challenges, accessible evidence-based prevention practices (EBPPs) are critical. In the USA, schools are the primary setting for children’s SEB service delivery. Still, EBPPs are rarely adopted and implemented by front-line educators (e.g., teachers) with sufficient fidelity to see effects. Given that individual behavior change is ultimately required for successful implementation, focusing on individual-level processes holds promise as a parsimonious approach to enhance impact. Beliefs and Attitudes for Successful Implementation in Schools for Teachers (BASIS-T) is a pragmatic, multifaceted pre-implementation strategy targeting volitional and motivational mechanisms of educators’ behavior change to enhance implementation and student SEB outcomes. This study protocol describes a hybrid type 3 effectiveness-implementation trial designed to evaluate the main effects, mediators, and moderators of the BASIS-T implementation strategy as applied to Positive Greetings at the Door, a universal school-based EBPP previously demonstrated to reduce student disruptive behavior and increase academic engagement.

**Methods:**

This project uses a blocked randomized cohort design with an active comparison control (ACC) condition. We will recruit and include approximately 276 teachers from 46 schools randomly assigned to BASIS-T or ACC conditions. Aim 1 will evaluate the main effects of BASIS-T on proximal implementation mechanisms (attitudes, subjective norms, self-efficacy, intentions to implement, and maintenance self-efficacy), implementation outcomes (adoption, reach, fidelity, and sustainment), and child outcomes (SEB, attendance, discipline, achievement). Aim 2 will examine how, for whom, under what conditions, and how efficiently BASIS-T works, specifically by testing whether the effects of BASIS-T on child outcomes are (a) mediated via its putative mechanisms of behavior change, (b) moderated by teacher factors or school contextual factors, and (c) cost-effective.

**Discussion:**

This study will provide a rigorous test of BASIS-T—a pragmatic, theory-driven, and generalizable implementation strategy designed to target theoretically-derived motivational mechanisms—to increase the yield of standard EBPP training and support strategies.

**Trial registration:**

ClinicalTrials.gov ID: NCT05989568. Registered on May 30, 2023.

**Supplementary Information:**

The online version contains supplementary material available at 10.1186/s13012-023-01330-y.

Contributions to the literature
Evidence-based prevention programs are often not adopted or delivered with sufficient fidelity to address children’s social, emotional, and behavioral health needs, even when conducive organizational supports are in place.This study tests a parsimonious and pragmatic individually focused implementation strategy delivered to frontline professionals (teachers) to enhance their implementation of an evidence-based prevention program. We will evaluate the effects on proximal outcomes/mechanisms (e.g., attitudes) as well as implementation (e.g., adoption) and children’s outcomes (e.g., social, emotional, and behavioral status).Findings will fill a gap in the literature surrounding the utility of pragmatic, individual-level strategies for preventive interventions as well as the variables (mechanisms) through which the strategies operate, and under which conditions the strategies work.

## Background

### Addressing children’s social, emotional and behavioral health

At least one in five children experience social, emotional, and behavioral/mental health (SEB) challenges [1], making accessible SEB prevention and intervention programming a high priority. When children experience SEB challenges, they are at an increased risk of academic and social difficulties in school and long-term experience with the judicial system, substance use problems, and unemployment [1]. In contrast, children who receive preventive SEB support experience social and academic gains into adulthood [2–6]). Given the widespread need to address children’s SEB, exacerbated by the COVID-19 pandemic [7, 8], accessible prevention programming is a high priority.

### School-based prevention

Schools are the most common setting in which children and adolescents in the USA receive both preventive and indicated care for SEB concerns [9–11]. As a result, school-delivered SEB practices have increasingly been prioritized in policy and legislation [12–14]. In particular, there are a variety of universal evidence-based prevention practices (EBPPs) that exist to address children’s SEB challenges [15, 16]. Among these are high-quality, effective, universal EBPPs delivered at the classroom or school level to support student SEB health [17–20].

### Need for improved implementation supports

As with other service sectors, EBPPs for school settings are adopted inconsistently and frequently delivered with poor fidelity [21–23]. In the education sector, this implementation gap has been resistant to change despite intervention at federal and state policy levels [24]. Even studies of quality implementation strategies, such as coaching and consultation, demonstrate that many EBPPs fail to be adopted by school-based implementers [25–27]. As a result, the potential public health impact of SEB-focused EBPPs is greatly diminished [28].

### Implementation determinants in schools

Like other health service sectors, schools are multi-level implementation contexts with myriad priorities, decision-makers, implementers, and recipients of the intervention. Across sectors, organizational influences on implementation have been the subject of considerable research, but creating organizational change is time-consuming and expensive, often lasting years [29]. Furthermore, even with appropriate implementation support to address organizational-level barriers or enact organizational facilitators, educators’ EBPP implementation can still be stilted.

Most implementation frameworks include critical individual implementer factors [30, 31]. Indeed, front-line professionals—such as teachers—are ultimately responsible for the adoption and delivery of EBPPs and present their own set of implementation determinants such as attitudes, beliefs, and intentions to implement an EBPP [30, 32, 33]. Some school-based research has documented that individual-level determinants can be more predictive of EBPP implementation than organizational factors, such as climate or culture [32, 34], even within supportive implementation contexts [35, 36].

### Individual-level implementation strategies

Despite significant research on cornerstone implementation strategies such as training and consultation [37, 38], additional approaches are often needed to change behavior. Individual theories of behavior change can be leveraged to further facilitate EBPP use. The current study applies the theory of planned behavior (TPB) [39] and the health action process approach (HAPA) [40]. The TPB states that an individual’s *subjective norms* (their perceptions of the social importance of performing the behavior), *attitudes* (appraisals of the behavior), and *task self-efficacy* (perceived behavioral control and confidence in their ability to implement the behavior), cumulatively predict *intentions* to perform a behavior [41]. Intention is a strong predictor of behavior change [42–44]. The HAPA augments the TPB by (1) positing that the intention to engage in a behavior is influenced by one’s *outcome expectancies* and *perceived risks* (beliefs about the possible consequences of a behavior and risks of not engaging in a behavior, factors that we cluster with “attitudes” in the TPB) and (2) emphasizing individual *volition* (initial action planning and planning for coping with barriers) that increase an implementers’ maintenance self-efficacy (the belief that one is capable of overcoming barriers while implementing the behavior) and facilitate the link between intentions and behavior. The most common implementation strategies, such as workshops, coaching, and consultation, primarily target knowledge and skills while often neglecting to explicitly attend to norms, attitudes, intentions, and volition.

### Beliefs and attitudes for successful implementation in schools for teachers (BASIS-T)

BASIS-T is designed to address individual-level mechanisms of behavior change (e.g., self-efficacy) often missing from standard EBPP training that relate to motivation prior to receiving training and volition after training. It is an EBPP-agnostic implementation strategy designed to be delivered within the preparation/adoption phase, immediately prior to active implementation [45]. BASIS-T targets behavioral intentions via improvement in attitudes, subjective norms, and self-efficacy. Our theory of change (Fig. 1) shows the core BASIS-T components, mechanisms of change (volitional and motivational), implementation outcomes, and resulting child SEB outcomes within the current study. The BASIS-T strategy is grounded in the TPB and in the HAPA strategies of *action planning* (specifying the “when,” “where”, and “how” of implementing the EBPP) and *problem-solving planning* (generating solutions to specific barriers that one anticipates encountering when adopting a new practice) to overcome barriers to implementation.

**Fig. 1 Fig1:**
[figure not shown]
BASIS-T theory of change: components, hypothesized mechanisms of change and target outcomes

#### Preliminary BASIS-T studies

The BASIS strategy was developed via an iterative user-centered design approach [46]. Initial pilots of BASIS-T and a version designed for school-based mental health clinicians (BASIS-C) have demonstrated promise in enhancing participants’ attitudes, subjective norms, self-efficacy, and adoption [30, 33, 47]. The BASIS-T pilot study on which the current project is based was an attention-control randomized trial conducted with 82 elementary school teachers implementing a universal, classroom-based EBPP [48–50]. That study found a statistically significant positive impact on implementation task self-efficacy and outcome expectancy immediately after training and significantly less decline in task self-efficacy than attention control throughout the academic year [33]. Positive attitudes towards evidence-based practices decreased for both groups over time but with a marginal time trend in favor of less decrease for the BASIS-T condition (*p* = 0.08). Except for ownership/role, all other mechanisms (outcome expectancies, subjective norms, self-efficacy, and intentions to implement) deteriorated for both groups after the post-BASIS timepoint (i.e., during active implementation), yet all effect sizes were in favor of less deterioration in the BASIS-T condition. Significantly higher proportions of teachers in BASIS-T immediately adopted the EBPP (74% of BASIS-T condition, 40% of attention control). With marginal significance, fidelity to the EBPP remained steady for the BASIS-T group over time but deteriorated for attention control (*p* = 0.052), and the BASIS-T condition engaged in the EBPP more frequently (*p* = 0.097). A preliminary analysis estimated the cost of BASIS-T at $256 per teacher based on time and material costs. Notwithstanding the promise of these findings, this was an underpowered pilot trial designed to lay a foundation for the current study.

### Objectives and aims

This project will conduct a hybrid type 3 effectiveness-implementation randomized trial to evaluate the effects of BASIS-T on implementation mechanisms and outcomes when applied to positive greetings at the door (PGD), a low-burden, universal EBPP that has been found to reduce disruptive behavior and increase academic engagement [51–53], both important indicators of positive SEB functioning [54–57]. We will also examine for whom, under what conditions, and how efficiently BASIS-T works to improve outcomes.

PGD is a preventive classroom management strategy based on three major themes: (a) classroom climate, (b) pre-correction, and (c) positive reinforcement [53]. PGD has been found to be well aligned with school settings and effective at addressing SEB needs. Multiple studies have found increases in on-task behavior in middle school students, and reductions in latency-to-task engagement in high school students [51, 52]. These findings were replicated in a longitudinal randomized controlled efficacy trial conducted with 203 students across 10 classrooms, finding improvements in academic engagement and decreases in disruptive behavior [53]. However, consistent with more general research on universal EBPPs, results also suggested that some of the teachers delivering PGD struggled with initial adoption, with two of the five teachers in the PGD condition (40%) requiring extra consultative support due to initial low levels of implementation.Aim 1: Experimentally evaluate the effects of BASIS-T versus active comparison control (ACC)

Aim 1 will evaluate the main effects of BASIS-T on proximal mechanisms (attitudes, subjective norms, self-efficacy, intentions to implement, and maintenance self-efficacy), implementation outcomes (adoption, reach, fidelity, and sustainment), and student outcomes (classroom aggregated grades, test scores, attendance, and teacher ratings of classroom on-task behavior, disruptive behavior, and prosocial behavior).*Research question (RQ) 1a.* Is BASIS-T more effective than the ACC condition at producing changes in proximal mechanisms of behavior change?*RQ 1b.* Is BASIS-T more effective than the ACC condition in promoting implementation outcomes?*RQ 1c.* Is BASIS-T more effective than the ACC condition in promoting meaningful changes in student SEB and academic outcomes?Aim 2: Evaluate how, for whom, under what conditions, and how efficiently BASIS-T works to improve outcomes

Aim 2 will evaluate the effects of BASIS-T on student outcomes via the mechanisms of implementation behavior change and if those effects are moderated by teacher factors and school contextual factors. We will also explore how mechanisms are linked to implementation outcomes for “hypothesis-defying residuals” (i.e., teachers whose attitudes, subjective norms, and self-efficacy surrounding EBPP implementation are inconsistent with their documented implementation behaviors).*RQ 2a*. Are the effects of BASIS-T mediated via mechanisms of behavior change?*RQ 2b*. Are the effects of BASIS-T on implementation and student outcomes moderated by teacher-level factors (e.g., demographics, stress, baseline intentions to implement) and school-level factors (e.g., geographic location, school demographics, supportive leadership, implementation climate)?*RQ 2c*. What explains “residual” teachers whose implementation behaviors are not accounted for by the mediation model?*RQ 2d.* What are the costs and cost-effectiveness of BASIS-T?

## Method

This hybrid type 3 effectiveness-implementation trial employs a blocked randomized cohort design with an active comparison control (ACC) condition to provide a rigorous initial test of the efficacy of BASIS-T in authentic elementary school settings (see Additional file 1 for SPIRIT checklist). Schools will be randomized to BASIS-T or ACC conditions (see Fig. 2) and data will be gathered at the teacher/classroom level. There will be two cohorts of participants—one for each of two academic years—and multiple time points of data collection over 18 months across implementation and sustainment phases. Institutional review board approval has been obtained (Additional file 2), which includes plans for de-identification and secure data storage as well as tracking and reporting of adverse events or protocol modifications if needed.

**Fig. 2 Fig2:**
[figure not shown]
CONSORT diagram

### Participants and recruitment

Teachers from schools in the USA will be recruited to participate. Inclusion criteria include being a teacher at an elementary (typically K–5th grade or K–8th) school and not having been trained or supervised in delivering PGD in the past 5 years. We will recruit approximately 276 teachers from 46 elementary schools in the USA. The final balance of teachers and schools is dependent on recruitment, with the goal of meeting minimum statistical power. Schools will be approached to participate via multiple routes, including leveraging existing relationships and networks, educational listservs, and posting on social media. Interested school representatives may respond using the interest survey linked in flyers or by contacting the research team via email. The generalizer (generalizer.org), a free, web-based tool for selecting schools for randomized controlled designs that are statistically representative of a chosen inference population, will also be used to help assure the representativeness of our sample [58]. Strata will be created on urbanicity, school race/ethnicity, school percent female, school percent free and reduced lunch, school size, school percentage English language learners, and the number of schools in the district.

Once schools have been selected, teacher recruitment will proceed for both cohorts of schools with the assistance of site administrators. Principals will provide us with the email addresses of teachers in their schools. Research staff or school leadership will contact eligible participants by email or phone to describe the purpose of the study, research procedures, and incentives. Informed consent will be collected online prior to training (Additional file 3) and teachers will be free to decline participation. Monetary incentives will be provided to participating teachers and schools.

### Randomization

This study will employ a randomized cluster-blocked cohort design with random assignment at the school level to eliminate the possibility of condition contamination among teachers. Schools will be blocked within the district by a number of teachers participating in the study, school enrollment, % of non-White students, % of students who qualify for free/reduced lunch, and mean teacher baseline BASIS-T mechanisms of change (e.g., self-efficacy). These variables were chosen because they are associated with EBPP use and student academic outcomes [59]. We will create matched pairs using the nearest neighbor approach [60] and randomly assign schools within pairs to condition. Randomization will occur to the greatest extent possible, although there may be some situations where trainers in only one condition are available when school staff are available to be trained; these situations will be considered essentially random. School personnel and participants will be masked to condition.

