#### Data analytic plan

Basic data screening and descriptives will be conducted for all quantitative variables. We will explore and statistically adjust for baseline equivalence between conditions on all individual outcomes and all school, teacher, and student variables following established guidelines [83]. For all longitudinal modeling, the statistical adjustment will use baseline intercepts as random terms; for dissimilar outcome domains, non-equivalent baseline variables will be included as covariates. Data missing at random will be modeled using full information maximum likelihood estimation or multiple imputation as appropriate.

Unless otherwise indicated, quantitative analyses will employ mixed-effects models using time points nested within classrooms within the school. Standard model-building procedures will be used [84, 85]. Classroom and time trends will be allowed to randomly vary. Piecewise time models will estimate slopes from T1 to T4 (training), T5 through T6 (first month of post-training implementation), T7–T11 (first academic year), and T12–T13 (sustainment during the subsequent year). Variables for condition and condition x time will be added, and iterative models with possible control variables will be tested. Covariates not contributing at *p* < 0.10 based on likelihood ratio tests will be removed. Level 2 and 3 predictors will be fit and excluded for the same reasons. We will obtain estimates of whether there were statistically significant differences among the groups on the rate of change over time (i.e., slope) and whether there are statistically significant group differences in the average score on each outcome variable at the final timepoint of each piecewise segment. Models will be generalized, with appropriate link functions (e.g., log-link, Poisson) applied based on distributional form (e.g., dichotomous, zero-inflation). Estimation will be fit using full maximum likelihood. Models will be assessed for possible violations of assumptions. Goodness-of-fit will be evaluated using likelihood ratios, deviance statistics, and fit criteria. The inference will be evaluated relative to *p* < 0.05. For RQs with multiple DVs, we will adjust for the false discovery rate using Benjamini and Hochberg’s procedure [86].

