We will use thegeneralizer.org to compare our sample to national demographics to examine the generalizability of our findings [58]. If not generalizable, we will use inverse probability weighting to increase the representativeness of estimates [87].*RQ 1a*: A series of 3-level piecewise mixed effects models will be used to test our primary hypotheses: (1) the BASIS-T condition will show steeper gains than the ACC condition from T1 to T2 (e.g., more favorable attitudes towards EBPPs, increased social norms; enhanced task and maintenance self-efficacy; stronger intentions to implement) and (2) both groups will decline after training (T3–T5) as has been found in past TPB research [88], and in the BASIS-T pilot trial [33], but the BASIS-T condition will have longer sustained between-condition effects after training from T3 to T13. Dependent variables will include subscale scores on attitudes, social norms, self-efficacy, intentions, and maintenance self-efficacy.*RQ 1b*: BASIS-T impact on behavioral implementation outcomes will be tested in two ways. First, a mixed effects model will examine whether the proportion of teachers in the BASIS-T condition who adopt PGD (i.e., initiate PGD) is higher than the proportion in the ACC condition. Second, Kaplan–Meier time-to-event analyses will be used to compare conditions on the number of days between training and PGD initiation. Reach will be analyzed using mixed effects models comparing BASIS-T vs. ACC on the proportion of students in each classroom (out of those eligible based on whether their classroom teacher participated in PGD training) who received PGD practices. Impact on PGD fidelity will be analyzed using mixed effects models with sessions within teachers, testing for the main effects of condition on adherence and participant responsiveness ratings derived from both PGD observational and self-report fidelity data. We will test the effects of BASIS-T on PGD sustainment and delayed implementation using the multilevel longitudinal analytic approach described for RQ1a.*RQ1c*: BASIS-T impact on student SEB and academic outcomes will be tested via mixed effects multilevel models as described in RQ1a, with academic data aggregated to the classroom level. Dependent variables will include post-intervention scores on teacher ratings of student behavior.*RQ2a*: Whether mechanisms of behavior change mediate the impact of BASIS-T on implementation outcomes will be analyzed using path analysis [89] extending traditional mediation modeling to a multi-level framework for nested data [90, 91].*RQ2b*: To test whether the effect of BASIS-T on implementation and student outcomes is moderated by teacher factors (e.g., demographics, baseline intentions to implement) and school-level factors, we will add moderators and interaction terms to the analytic approach described in RQs 1a-c.*RQ2c*: To explore what explains “residual” teachers whose implementation behaviors are not accounted for by the mediation model, we will analyze qualitative interviews with teachers who have a difference between predicted (based on BASIS-T putative mechanisms) and actual implementation behavior of ≥ 1 SD. Data will be coded using an integrated directed and conventional content analysis [92] approach as certain codes will be conceptualized during the interview guide development and driven by the exploration, preparation, implementation, sustainment [93] framework (i.e., deductive approach) which will allow for the examination of influences on implementation across multiple levels and phases. Other codes will be developed through a close reading of an initial subset of transcripts (i.e., inductive approach). These themes will provide a way of identifying and understanding the most salient factors that impact implementation and extend beyond the existing BASIS-T mechanisms and theory of change. After a stable set of codes is developed, a consensus process will be used in which all reviewers independently code and compare their coding to arrive at consensus judgments through open dialogue [78, 79, 94].*RQ2d*: We will process cost data by assigning monetary values to each cost. We will use CostOut [95], a web-based program for conducting cost-effectiveness analysis in education, to identify nationally representative unit prices for ingredients. For qualitative data, we will rapidly analyze responses on an ongoing basis [96, 97] and incorporate newly identified costs into future surveys for quantitative measurement.

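### Schools are randomised in matched pairs, but the stated models have no pair term and the p < 0.10 rule can delete the matching variables, so standard errors and power are not guaranteed to reflect the design

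*Protocol article*

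**What the plan says.** The protocol article describes the allocation under Randomization. Schools are blocked within district on five kinds of variable: "Schools will be blocked within the district by a number of teachers participating in the study, school enrollment, % of non-White students", the percentage of students qualifying for free or reduced lunch, and the school's mean baseline level on the BASIS-T mechanisms. It gives the reason for choosing them: "These variables were chosen because they are associated with EBPP use and student academic outcomes". The allocation step is then explicit: "We will create matched pairs using the nearest neighbor approach [60] and randomly assign schools within pairs to condition".

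Under Data analytic plan the model is stated as: "quantitative analyses will employ mixed-effects models using time points nested within classrooms within the school". For RQ1a the same structure is repeated: "A series of 3-level piecewise mixed effects models will be used to test our primary hypotheses". No pair, block or district term is named in either place.

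Covariate handling is also fixed: "Covariates not contributing at *p* < 0.10 based on likelihood ratio tests will be removed", followed by "Level 2 and 3 predictors will be fit and excluded for the same reasons". A separate sentence in that section promises statistical adjustment for baseline non-equivalence on school, teacher and student variables, so the matching variables have more than one way into the model. Nothing says that they stay there.

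**The concern.** The design and the analysis are each stated clearly, and they do not fit together. Matching schools on prognostic variables makes the two schools of a pair alike, which lowers the true variance of the treatment difference. A model that contains neither the pairs nor the matching variables leaves that shared variance in its error term. Its standard error is then too large for the design that was run.

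The removal rule makes this unpredictable. Whether a matching variable is kept depends on its p value in the trial's own outcome data, from only 46 schools, and is decided separately for each outcome. Two outcomes in the same research question could be analysed with different adjustment sets, one recovering the gain from matching and the other not.

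At stake are precision and power that the design has already paid for, and a treatment estimate whose adjustment is settled after the data are seen.

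**Working it through.** **Inputs from the article (Power; Randomization; Data analytic plan).** J = 46 schools, evenly allocated, so 23 pairs if all are paired; n = 6 teachers per school after attrition; school ICC 0.10; alpha 0.05; stated minimum detectable effect size (MDES) d = 0.37.

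**Assumptions.** Two-sided test; power 0.80 for the main-effect MDES; total variance 1; one measurement per teacher. The share r of between-school variance that the two schools of a pair have in common is not given, so it is varied.

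**1. The plan's own figure.** With no pairing effect,

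SE = sqrt[(ICC + (1 − ICC)/n) / (J/4)] = sqrt[(0.10 + 0.15)/11.5] = 0.147.

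On 44 df the multiplier is t(0.975) + t(0.80) = 2.865, so MDES = 2.865 × 0.1474 = 0.422, and power at d = 0.37 is 69%. The stated 0.37 does not follow from these inputs in a two-level formula. It can be reached with inputs the article does not list, for example a teacher-level variance share of about 0.5 in a repeated-measures formula (0.367). That is a separate matter and does not show that 0.37 is wrong.

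**2. Pairs and matching variables both absent.** The true SE under matching is sqrt[(0.10(1 − r) + 0.15)/11.5], while the unpaired analysis still reports about 0.147. Type I error and unpaired power come from simulating school means in 23 pairs (unpaired t, 44 df). Paired figures use 22 df and a multiplier of 2.932.

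| r (assumed) | True SE | Reported / true SE | Type I error, unpaired | Power at 0.37, unpaired | Power at 0.37, paired | MDES, paired |
|---|---|---|---|---|---|---|
| 0 | 0.147 | 1.00 | about 5% | 69% | 67% | 0.432 |
| 0.25 | 0.140 | 1.05 | 3.9% | 70% | 72% | 0.410 |
| 0.50 | 0.132 | 1.12 | 2.9% | 71% | 76% | 0.387 |
| 0.75 | 0.123 | 1.20 | 2.0% | 72% | 82% | 0.362 |

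The nominal unpaired MDES is 0.422 in every row.

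**3. How often the rule drops a real predictor.** A covariate explaining 10% of between-school variance explains 0.10 × 0.10/0.25 = 4% of the variance of school means. With 46 schools it misses p < 0.10 about 61% of the time. One explaining 20% misses it about 37% of the time.

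**4. The rule applied to five matching variables.** Simulation: 4,000 runs, nearest-neighbour pairs on five independent covariates, backward deletion at p ≥ 0.10, the covariates together explaining 30, 50 or 80% of between-school variance.

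| Analysis | Type I error | Power at d = 0.37 |
|---|---|---|
| No covariates, no pairs | 3.8 / 4.2 / 3.3% | 68 / 70 / 70% |
| Pruned at p < 0.10 | 4.9 / 6.2 / 6.1% | 73 / 78 / 82% |
| All five forced | 4.3 / 5.3 / 5.1% | 71 / 77 / 82% |
| Pair analysis, 22 df | 4.6 / 5.4 / 5.4% | 69 / 74 / 76% |

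On average 1.6, 2.3 and 3.2 of the five covariates survive, and after pruning the reported SE is about 3 to 5% too small. Monte Carlo error on the type I figures is about 0.35 points. Both simulations use school means and a linear outcome, so they are indicative only.

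**The case against.** The strongest reply has four parts.

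- **This is a condensed article.** A pair intercept could be left to an analysis plan that is not shown, and the model sentence allows for exceptions. That would answer silence. Here the article states both the model levels and a removal rule, and the rule as written reaches the matching variables. The objection lowers confidence that the final analysis will lack a pair term; it does not remove the conflict in the text.
- **The matching variables may enter anyway**, as control variables or through the baseline non-equivalence adjustment, and those that survive recover precision. This stands. In step 4, pruned covariates gave more power than a pair analysis, although part of that edge comes from standard errors that are slightly too small. The penalties in step 2 apply only when no matching variable is retained.
- **The first RQ1a hypothesis concerns steeper gains.** Stable differences between schools largely cancel from change over time, so the step 2 penalties do not carry over to slope tests. This also stands. They apply to end-of-segment contrasts and to outcomes measured once.
- **The size rests on an assumed r.** True. At r = 0 there is no penalty, and a pair analysis on 22 df is slightly worse (MDES 0.432 against 0.422).

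A reader might infer that the matching is wasted. It is not: it still balances the arms and lowers the true variance, whether or not the model gives credit for it. A reader might also infer that leaving out the pairs produces false positives. The error runs the other way.

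**Conclusion.** The point holds in a limited form. The article randomises within matched pairs, states models without a pair term, and allows the matching variables to be deleted outcome by outcome. For end-of-segment contrasts and outcomes measured once, the reported standard errors and power are therefore not guaranteed to reflect the design.

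If neither pairs nor matching variables are in the model, at ICC 0.10 and with pairing assumed to explain 25 to 75% of between-school variance, the standard error is 5 to 20% too large and 2 to 10 points of power at d = 0.37 go unused. The test is conservative in that case. If some matching variables survive pruning, the loss is smaller or absent, and the remaining fault is an adjustment set chosen from the outcome data, with mild optimism in the standard error.

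A reader might go further and infer materially inflated type I error from full maximum likelihood with many school-level covariates. The article states neither the reference distribution for the tests nor how many such covariates would be retained, so it does not support that reading. The issue is worth correcting because the remedy is nearly free, but it does not threaten the validity of the trial.

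**What to change.** For the RQ1 models, prespecify one or both of the following as forced terms:

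- a matched-pair term, preferably a random intercept;
- the school matching variables, together with the baseline value of the outcome or mechanism where one is collected (teacher ratings of student behaviour start only at time 4, so they have no time 1 value).

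State that these terms are the same for every outcome in a research question and are exempt from the p < 0.10 removal rule. Other covariates can still be handled as planned.

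The cost is wording in the analysis plan. The matching variables must be in hand before schools can be paired, so no new data are needed. The statistical price is a few degrees of freedom for forced covariates. At most, fixed pair effects cut the df from 44 to 22 and raise the MDES multiplier from 2.865 to 2.932, about 2%; a random pair intercept limits that loss. If pairing turns out to explain nothing, the result is slightly less power than the unpaired model (67% against 69% at d = 0.37).
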